### Clinical Setting

The QPL will be developed in the following two clinical contexts, which are prone to cancer resistance, and contrasted in terms of epidemiology, life expectancy, long-term treatment options, and expected effectiveness: (1) triple-negative and luminal B metastatic breast cancer (MBC) and (2) metastatic uveal melanoma (MUM), both within the first 3 lines of anticancer treatment after treatment resistance has occurred.

Triple-negative and luminal B MBC represents approximately 15% and 50% of all breast cancer cases, respectively [67], and recurs with distant metastasis in approximately 30% of early-stage patients [68]. MBC is an incurable disease, with a median overall survival of 3 years and a 5-year survival rate of 25% [69]. Patients with MBC are generally followed by their oncologist for years, punctuated by occurrences of treatment resistance for which a new treatment regimen may be offered. This implies successive disclosures of the progressing disease and discussions of alternative treatment regimens [70].

Uveal melanoma is a rare cancer [71]. Up to 50% of patients with uveal melanoma develop metastases, mostly in the liver, within a median time of 2 to 3 years [72]. Once metastasis occurs, the median overall survival ranges from 9 to 12 months because of the lack of effective treatment options [73]. Most patients with MUM are referred to a medical oncologist after a multidisciplinary tumor board meeting. Medical oncologists then inform patients about metastatic progression and possible treatment alternatives. The dismal prognosis and rapid evolution of the disease are challenging aspects in the communication between oncologists and patients. A discrepancy in knowledge appears when the medical oncologist is aware of the patient’s poor prognosis while the patient is still in good shape and does not expect such quick, fatal outcomes.

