##### Quantitative Assessment

Standardized questionnaires will be completed by patients to describe their unmet information and support needs while facing cancer resistance in the MBC and MUM settings. These questionnaires will also be used to obtain preliminary data, albeit limited to the potential clinical usefulness of the designed QPL. This will be performed by comparing responses from patients at step 1b (QPL-naive group) with clinically similar patients at step 2 (QPL intervention group).

As information needs may depend on patients’ characteristics [10,18], these outcomes will be assessed according to patients’ sociodemographic (ie, age, gender, educational level, and marital status) and psychological correlates (ie, beliefs, preference for information, level of distress, and coping strategies). To address these outcomes and correlates, patients will be invited to complete standardized questionnaires, as detailed in Table 3.

**Table 3 table3:** Standardized questionnaires.

Measures of QPL^a^ potential clinical benefits			Factors assessed

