#### Quantitative Data

Statistical analyses will be conducted using SPSS software (version 27.0; IBM Corp). Standardized questionnaires used in steps 1b and 2, and the Delphi surveys, will be analyzed descriptively in terms of missing data, response frequency, mean and SD, median, and range.

In step 1b, responses to items of the PTPQ, EORTC QLQ-INFO25, and SCNS-SF34 will determine the prevalence of communication needs in the cancer resistance setting and thus help prioritize communication issues to compose the QPL.

The step 1b group (QPL naive) will comprise a historical control of patients from step 2 (QPL intervention group). Quantitative data collected from standardized questionnaires at step 1b will be compared with the data collected at step 2. Patients will be consecutively included in steps 1b and 2; therefore, they are expected to be clinically similar; however, sociodemographic and clinical data between these groups will be compared to check their similarity. Bivariate analyses of outcome measures will be performed to preliminarily assess the potential clinical usefulness of the QPL. Bivariate analyses will also be performed to explore patients’ satisfaction with information and support needs in relation to their sociodemographic and psychological characteristics (distress and coping strategies) in step 2 samples, overall and by cancer site.

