## Discussion

### Principal Findings

This protocol describes a study using an innovative, sequential, mixed methods approach and involving patients as well as oncology professionals to collaboratively develop a QPL for cancer resistance in the French cultural context.

This study will be undertaken in 2 clinical settings prone to cancer resistance and contrasted in terms of epidemiology, life expectancy, long-term treatment options, and expected effectiveness. The resulting QPL is expected to comprise core issues related to the cancer resistance context to which specific issues will be added if needed, according to the tumor site. The core QPL is expected to be applicable in other advanced cancer contexts.

QPLs seem effective in raising patients’ asking questions [38,42,94]; however, a complementary coaching intervention may be needed to further patients’ support [95,96,97]. Coaching is the provision of nondirective support by an individual (either in-person or remotely eg, by telephone or the internet) [98]. It is expected to help patients assess their information needs (ie, about treatment options such as disease-targeted treatment [standard or experimental], best supportive care, watchful waiting, and their benefits and harms) [18], prepare and rehearse questions [33], express their concerns or emotions [99], and prioritize issues to discuss during the consultation.

This study’s sequential collaborative mixed methods approach is innovative; the following methodological aspects are expected to be fruitful. First, a triangulation of perspectives is foreseen as it involves patients, clinicians, and researchers, and thus a better grasp of the specific realities of oncology consultation communication in resistant cancer care.

Second, the quantitative and qualitative data collection approaches are complementary, and the results will be sequentially and iteratively integrated. In-depth interviews with different protagonists who are experts in cancer resistance at their own level are expected to increase the appropriateness and acceptability of the tool. Considering the modalities and procedures of tool implementation from the outset is also meant to promote its adoption in routine practice. Focus group discussions and exploratory quantitative analyses will help decide for whom, when, and how the QPL will be implemented in clinical routine.

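### The pooled step 2 correlate analyses take no account of cancer site, so site can confound them, most of all for gender; the by-site analyses avoid this, but the plan does not say which result governs

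*Protocol article*

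**What the plan says.** The Quantitative Data part of the Data Analysis section fixes the method for the correlates. The wording is "Bivariate analyses will also be performed to explore", so the method is named and not left open. The outcomes are support needs and how satisfied patients are with what they were told, and these are to be examined "in relation to their sociodemographic and psychological characteristics (distress and coping strategies) in step 2 samples, overall and by cancer site". Each characteristic is thus related to the outcome one at a time, first in both cancers together and then in each. No adjustment for site is stated for the pooled version, and no rule says which version is interpreted if the two disagree.

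The Quantitative Assessment part of step 1b lists the sociodemographic correlates: "ie, age, gender, educational level, and marital status". Gender is therefore one of the characteristics to be examined.

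The Clinical Setting section says that the two cancers are "contrasted in terms of epidemiology, life expectancy, long-term treatment options, and expected effectiveness". It describes MBC as a disease "with a median overall survival of 3 years and a 5-year survival rate of 25"%, and gives a median survival of 9 to 12 months for MUM. Table 2 plans 40 patients per site in step 2, 80 in all.

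On use, the Principal Findings section of the Discussion says that, together with the focus groups, "exploratory quantitative analyses will help decide for whom, when, and how the QPL will be implemented in clinical routine".

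**The concern.** A crude association in a pooled sample mixes two things: the association within each cancer, and the difference between the cancers. The second part enters whenever both the outcome and the characteristic differ by site. The outcomes here concern information about disease and treatment, and psychological and support needs. The sites differ in prognosis and treatment, and the protocol itself expects some site-specific content in the question prompt list (QPL). A site difference in these outcomes is plausible, although it is not documented.

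Gender is the characteristic most likely to be spread unevenly. If MBC patients are nearly all women, nearly every man in the pooled sample has MUM, and a comparison of men with women becomes in part a comparison of MUM with MBC.

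At stake is a report that men, or some other subgroup, have different needs when the difference belongs to the cancer. That could colour the judgement about for whom the QPL is used. It also would not carry over to other advanced cancers, where the article expects the core list to apply.

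**Working it through.** The plan states no effect size, significance level or power for these analyses, so there is no figure of its own to reproduce beyond the sample size: 40 + 40 = 80, which agrees with Table 2.

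**Inputs from the article:** 40 MBC and 40 MUM patients; bivariate analysis; gender among the correlates.

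**Assumptions, not in the article:** no men among 40 MBC patients; 20 men among 40 MUM patients (range 16 to 24); no true gender effect; within-site SD of 1; a MUM–MBC outcome difference of d SD; a two-sided 5% test.

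**Bias of the crude gender difference.** Bias = d × (share of MUM among men − share of MUM among women).
- 20 men in MUM: men 20/20, women 20/60. Bias = d × (1 − 0.333) = 0.67d.
- 16 men in MUM: women 24/64. Bias = d × (1 − 0.375) = 0.625d.
- 24 men in MUM: women 16/56. Bias = d × (1 − 0.286) = 0.714d.

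**False-positive rate of the pooled t test** (5,000 simulated studies per row and sex mix):

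| Site difference d (SD) | Spurious gender difference, 20 men in MUM (SD) | False positives, 20 men in MUM | Range, 16 to 24 men in MUM |
|---|---|---|---|
| 0 | 0 | about 4% | 5% |
| 0.2 | 0.13 | about 9% | 7% to 9% |
| 0.5 | 0.33 | about 24% | 18% to 30% |
| 0.8 | 0.53 | about 49% | 38% to 60% |

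The first row is the nominal 5% apart from simulation error. One man in MBC changes little: at d = 0.5 the bias is 0.5 × (20/21 − 20/59) = 0.31 SD, with about 21% false positives.

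**After accounting for site.** In the same simulations a linear model with gender and site, and a t test within MUM alone, both reject in about 5% of studies for every d.

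**How far gender and site can be separated** (20 men in MUM):
- Correlation between gender and site: phi = (20 × 40 − 20 × 0) / √(40 × 40 × 20 × 60) = 800/1,386 = 0.58.
- Variance inflation: 1/(1 − 0.58²) = 1.5.
- Standard error of the site-adjusted gender effect: √(1/20 + 1/20) = 0.32 SD.
- Difference detectable with 80% power within MUM: (1.96 + 0.84) × 0.316 = 0.89 SD.

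Gender can be estimated, but imprecisely.

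**Other correlates.** For a continuous characteristic that differs by c SD between sites and has no true association within site, the spurious correlation is r = (cd/4) / √[(1 + c²/4)(1 + d²/4)].
- c = d = 0.5: 0.0625/1.0625 = 0.06; about 8% false positives.
- c = d = 0.8: 0.16/1.16 = 0.14; about 24% false positives.

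**Precision of the by-site analyses.** By the Fisher approximation, 80% power at 5% needs r of about tanh(2.80/√77) = 0.31 with 80 patients, and tanh(2.80/√37) = 0.43 with 40. A pooled association that fades within site may therefore reflect confounding, or only the smaller sample. The crude pooled and by-site results do not settle which.

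**The case against.** The strongest reply is that the same sentence already plans the analyses "in step 2 samples, overall and by cancer site". Within one cancer, site is constant and cannot confound. For gender, the MUM analysis is exactly the estimate one would want; with no men in MBC, a site-adjusted gender coefficient draws on the same MUM contrast. This stands, and it reduces the point to the pooled estimate and to the missing rule on which result governs.

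A reader might infer that gender and site are almost inseparable. The figures do not support that: phi is 0.58 and the variance inflation 1.5, with men and women both present in MUM under the assumed mix. The cost is precision, not loss of the estimate. A reader might also infer that all the correlates are badly distorted. For continuous ones the bias is modest unless both the characteristic and the outcome differ strongly by site.

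The size rests on a sex mix and a site difference that the article does not give, and the false-positive rates presuppose a 5% test that it does not state. The article also expects a common core of issues across both cancers, so the site difference in these outcomes could be small. All of this stands.

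Finally, the analyses are called exploratory, and a condensed article may leave modelling detail to a fuller plan. The exploratory purpose lowers the weight. The second argument is only partly met: the article does not leave the method open, but names bivariate analysis for the pooled sample.

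**Conclusion.** The point holds for the pooled analysis. As stated, it is crude across two cancers selected for contrast, and its associations can be confounded by site. The clearest case is gender, where under the assumed sex mix two thirds of any site difference would pass as a gender difference. The bias scales with d and vanishes at d = 0.

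It would go too far to say that the study will mistake site for gender, or that the result would misdirect implementation. The sentence on implementation names neither gender nor this analysis, and puts the focus groups beside the quantitative work; a reader would also have to overlook the by-site tables. What the documents support is an avoidable ambiguity of minor weight: an unadjusted overall estimate, a less precise but site-free alternative, and no statement of which one is to be interpreted.

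**What to change.** In the Quantitative Data section, replace the crude overall estimate with one model per characteristic on the pooled step 2 sample with cancer site as a covariate, or an equivalent site-stratified estimate or partial correlation. State that this is the overall result to be interpreted. Take the gender result from the MUM by-site analysis already planned, and report it with its confidence interval because it will be imprecise. Keep the by-site tables; they also show whether an association looks similar in the two cancers, which the adjusted model assumes.

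The cost is a sentence or two of text and one degree of freedom per model. Cancer site is known for every patient, so no new data are needed. The adjustment does not make the gender estimate more precise; it only stops a site difference from entering it.

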## Results

This study received grants from the Ile-de-France CancerôPole (2019-1-EMERG-14-ICH-1; March 2019) and from the *Fondation de France* (2019 number 00101610; December 2019) and was approved by the French national ethics committee in July 2019. As of December 2020, to reach data saturation, 26 oncology professionals’ interviews have been conducted and analyzed. As of October 31, 2021, a total of 40 and 31 patients with MBC and MUM have been recruited, 20 and 20 have been interviewed, and 39 and 28 have completed questionnaires, respectively.

## Discussion

### Principal Findings

This protocol describes a study using an innovative, sequential, mixed methods approach and involving patients as well as oncology professionals to collaboratively develop a QPL for cancer resistance in the French cultural context.

This study will be undertaken in 2 clinical settings prone to cancer resistance and contrasted in terms of epidemiology, life expectancy, long-term treatment options, and expected effectiveness. The resulting QPL is expected to comprise core issues related to the cancer resistance context to which specific issues will be added if needed, according to the tumor site. The core QPL is expected to be applicable in other advanced cancer contexts.

QPLs seem effective in raising patients’ asking questions [38,42,94]; however, a complementary coaching intervention may be needed to further patients’ support [95,96,97]. Coaching is the provision of nondirective support by an individual (either in-person or remotely eg, by telephone or the internet) [98]. It is expected to help patients assess their information needs (ie, about treatment options such as disease-targeted treatment [standard or experimental], best supportive care, watchful waiting, and their benefits and harms) [18], prepare and rehearse questions [33], express their concerns or emotions [99], and prioritize issues to discuss during the consultation.

This study’s sequential collaborative mixed methods approach is innovative; the following methodological aspects are expected to be fruitful. First, a triangulation of perspectives is foreseen as it involves patients, clinicians, and researchers, and thus a better grasp of the specific realities of oncology consultation communication in resistant cancer care.

Second, the quantitative and qualitative data collection approaches are complementary, and the results will be sequentially and iteratively integrated. In-depth interviews with different protagonists who are experts in cancer resistance at their own level are expected to increase the appropriateness and acceptability of the tool. Considering the modalities and procedures of tool implementation from the outset is also meant to promote its adoption in routine practice. Focus group discussions and exploratory quantitative analyses will help decide for whom, when, and how the QPL will be implemented in clinical routine.

Third, the quantitative assessment allows the assessment of the specific information and support needs that are experienced when faced with cancer resistance. These data may be compared between 2 groups: before (step 1b) versus after (step 2) the availability of the QPL. This will offer initial information on the clinical utility of the tool tailored to cancer resistance in the French cultural context.

Owing to consecutive sampling, information will be available about the number of patients willing to use the QPL and the number of oncologists who will engage in its use during consultations [92]. Furthermore, the resulting QPL will be pilot-tested on outcomes such as patients’ beliefs about primary cancer treatment goals or satisfaction with the information provided about prognosis and treatment, which are important [93] and previously lacking effect measurement of QPL use [2].

Finally, focus group discussions will specifically elicit collaborative work. The reactions and proposals of various appropriate persons [100] will help prepare the modalities of QPL use in routine practice and promote its long-term adoption [101], that is, the tool use in real-world clinical practice [102]. Moreover, the Delphi process aims to reach consensus among patients and oncology professionals on a QPL version 1 and explicit guidance for clinical implementation [103,104]. We anticipate that these persons will have diverging views and opinions about the tool [91]; thus, a consensus will have to be developed.

This protocol has several limitations. The methodology described herein is an innovative but long process. It may not be systematically applied as a new clinical context in need of a QPL. However, this study offers the opportunity to reveal unnecessary steps and thus indicate an optimized process for future research.

We focus on the communication between oncologists and patients; however, other oncology professionals such as nurses or psychologists may also play an important role in responding to patients’ information and support needs; therefore, further research is needed to address their specific role in addressing these needs. In addition, patients’ relatives may also present their specific information and support needs and may interact with the patient when facing this information. The QPL may also be useful to them, as such or adapted, and this must be evaluated.

The assessment of patients at step 1b and step 2 of this study is cross-sectional; therefore, we also need to consider that information is not collected on the same individual patients over their evolving needs and information processing.

### Dissemination

A clinically and culturally specific QPL complemented, if necessary, by a coaching intervention is expected to facilitate patients’ participation in oncology consultations to improve oncologists’ responses to their information and support needs. This tool allows patients to control the provided information according to their wishes and thus respects their potential ambivalence and need for hope. Digital health interventions provide patients with evidence-based interventions through software apps. The availability of QPLs through these technologies is increasing [55,105,106]. Digital health interventions are easily accessible to patients from their homes through mobile devices or websites. Studies suggest that they are cost-effective, increase uptake by patients and clinicians, and provide clinical benefits [107]. Therefore, this French-adapted QPL will be available not only in paper form (brochure) but also as an app (MyCurie app) and on the institutional website. It will contain information about the purpose, interests, and modalities of use of the brochure or web document. Moreover, studies have shown the importance of clinicians’ endorsement of the tool, encouraging its use by patients; therefore, particular attention will be given to an implementation guide that recommends communication about this tool during the consultation. Patient and partner representatives of the Institut Curie will be invited to attend the local public and scientific conferences planned to communicate about this study. They will be solicited for their feedback on articles to disseminate results nationally and internationally through popular or scientific journals.

### Conclusions

This research proposes an original methodology to adapt and further develop a QPL for patients with resistant cancer and enable its implementation in the French cultural context. It is expected to facilitate patients’ expression of questions, concerns, and emotions and, in that way, improve oncologists’ responses to their information and support needs. Clinically, this study will also improve the understanding of patients’ and clinicians’ experiences, difficulties, obstacles, and strategies in discussing prognosis and treatment options in the first anticancer treatment lines after cancer resistance has developed. Methodologically, it will be possible to infer an efficient method for designing and guiding the implementation of communication aids for patients with advanced cancer.

## Abbreviations

EORTC QLQ-INFO25: European Organization for Research and Treatment of Cancer Quality of Life Questionnaire–Information Module
HECTOR: Helping Patients Communicate With Oncologists When Cancer Treatment Resistance Occurs
MBC: metastatic breast cancer
MUM: metastatic uveal melanoma
PTPQ: Prognosis and Treatment Perception Questionnaire
QPL: question prompt list
REDCap: Research Electronic Data Capture; Vanderbilt University
SCNS-SF34: Supportive Care Needs Survey–Short Form
